### Community engagement and feedback

Prior to recruiting participants, we set up a specific community engagement structure. Its mission was to inform, sensitise and engage directly with the local population. Initially overseen by Médecins Sans Frontières France (MSF), World Vision was involved in the introduction of specific techniques, including mobile messaging.

Within each health area, Community Advisory Committees were constituted. They conducted initial meetings with local political and administrative leaders, social groups and organisations, local associations and other non-governmental organisations, and traditional and religious leaders, and their input was included in the planning of the trial implementation. We then conducted regular, separate discussion meetings with these different groups every 2 weeks to receive and integrate feedback on social harms, individual and community level risks, perceptions about the vaccine and the study, legal or administrative complaints and vaccination implementation issues.

### Eligibility, recruitment and enrolment

Using predefined eligibility criteria (box 1), we invited all adults and children aged 1 year or greater, including pregnant and breast feeding women, to participate if they lived or worked in the selected health zones and, at the time of vaccination, planned to remain there for 1 month post dose 2. Health workers were specifically encouraged to participate. We provided information about the study to local populations through the distribution of posters and flyers, banner displays in the target health areas, radio and television broadcasts and interviews during church gatherings and through interactive street visits using loudspeakers. Until the outbreak was declared over, we provided participants with information on where to present for care if they developed EVD symptoms and informed participants that they could still receive rVSV-ZEBOV-GP as recommended by WHO if eligible.^27^ We instructed Ebola Emergency Treatment Centres (ETCs) on how to report that a presenting patient had received Ad26.ZEBOV, MVA-BN-Filo. We required a parent or caregiver to accompany any child aged less than 18 years to the study vaccination site.

Box 1DRC-EB-001 inclusion and exclusion criteria for vaccinationInclusion criteriaMust provide a written or witnessed (if illiterate) informed consent form indicating that he or she understands the reasons for the study and is willing to participate in the study and to be vaccinated. If less than 18 years old, must have a parent or guardian that is able to meet this criterion.Must be aged 1 year or older.Must be healthy in the investigator’s clinical judgement as assessed on the day of vaccination.Must be willing to have a photograph taken.Must be available and willing to participate for duration of study visits and follow-up.Exclusion criteriaKnown history of Ebola virus disease (EVD).Has received any experimental EVD vaccine less than 1 month prior to visit 1.Known allergy or history of anaphylaxis or other serious adverse reactions to vaccines or vaccine products, egg and egg proteins or gentamicin.Presence of an acute illness (excluding minor illnesses such as mild diarrhoea or mild upper respiratory tract infection) or temperature ≥38.0°C at visit 1 (dose 1 visit). Participants with such symptoms will be temporarily excluded from vaccination at that time but may be rescheduled for vaccination at a later date if feasible (and if within 84 days of the first dose).Presence of significant conditions or clinically significant findings at the vaccination visit for which, in the opinion of the investigator, vaccination would not be in the best interest of the participant.History of recurrent generalised hives.

### Intervention delivery

We established six study vaccination sites within the participating health zones in Goma. Communicating in Swahili, French or a local dialect, Nande, we conducted symptom screening and a temperature check for possible EVD for participants at a triage desk before they could proceed into the clinic. We provided a short medical consultation to participants presenting at triage with fever and/or illness and including, if appropriate, a test for malaria, and treatment if positive, as well as free treatment for other minor illnesses according to national medical protocols. A postvaccination medical consultation was also offered for any participants complaining of illness during the observation period. We then referred participants to the nearest appropriate health facility if any further medical intervention was required.

At the first visit, delegated medical staff of the trial confirmed eligibility, explained the study aims and procedures, answered any questions, and sought informed consent (and informed assent for children aged 12–17 years), with witnessed consent for illiterate individuals. We offered urine pregnancy tests at the time of vaccination if a participant believed that she might be pregnant and/or if her last menstrual period was more than 1 month ago. We gave participants the Ad26.ZEBOV vaccination and asked them to remain at the site for 15 min to monitor for any immediate adverse effects. We provided participants with a laminated vaccination card with their photograph, which we asked them to present at subsequent visits. Enrolment and dose 1 vaccination took place between 14 November 2019 and 29 February 2020.

We collected data on place of residence and telephone numbers from all trial participants and contacted them through mobile phone calls and automated short message service (SMS) to remind them to attend for dose 2 and followed up, with home visits if these were needed. At the clinic visits for dose 2, similar triage, eligibility and health checks were conducted. Participants who attended more than 84 days post dose 1 were still able to receive the second dose until the study vaccination sites closed on 10 February 2021.

After the study start, all individuals presenting to an ETC, peripheral health facility or an EVD testing centre were expected to have their rVSV-ZEBOV-GP and Ad26.ZEBOV, MVA-BN-Filo vaccination status confirmed as part of routine data collection, with this information being recorded in the routine Ministry of Health EVD surveillance database. This included recording the participant identification (ID) number from the study vaccination card. If the patients were not able to present their cards at the ETC but mentioned being a study participant, ETC staff requested the family to bring the card to the ETC. For lost cards, we instructed ETC staff to collect the patient’s name, vaccination and clinic site details, and, if possible, the last vaccination date, and provide this information to the study data management team to retrieve the participant’s ID number and manually complete the ETC line-list.

Due to the waning EVD outbreak, the Trial Steering Committee decided to suspend dose 1 vaccination on 29 February 2020, after 20 427 participants had been vaccinated. Dose 2 vaccination continued, recognising that, while the objective of evaluating VE could no longer be met, the other objectives were still achievable. However, due to the COVID-19 outbreak in DRC, all study vaccinations were suspended from 10 April to14 September 2020, while special precautions to ensure the safety of participants and staff from COVID-19 were established. As a result of suspension of activities, the protocol was amended (10 August 2020, version 7.0) to include immunogenicity assessment of the impact of delayed dose 2 vaccination beyond 84 days post dose 1 and safety follow-up windows (table 3). Following implementation of infection control measures, vaccination continued and dose 2 delivery was completed on 9 February 2021.

In addition to the main study, we enrolled participants into three subsets, with consent sought in separate sections in the main study informed consent and assent forms (online supplemental appendixs 1–10):

10.1136/bmjopen-2021-055596.supp2Supplementary data

10.1136/bmjopen-2021-055596.supp3Supplementary data

10.1136/bmjopen-2021-055596.supp4Supplementary data

10.1136/bmjopen-2021-055596.supp1Supplementary data

10.1136/bmjopen-2021-055596.supp10Supplementary data

10.1136/bmjopen-2021-055596.supp9Supplementary data

10.1136/bmjopen-2021-055596.supp8Supplementary data

10.1136/bmjopen-2021-055596.supp7Supplementary data

10.1136/bmjopen-2021-055596.supp6Supplementary data

10.1136/bmjopen-2021-055596.supp5Supplementary data

Immunogenicity substudy: 57 non-pregnant adults and 90 children (54 children aged 4–11 years and 36 adolescents aged 12–17 years) were enrolled in an immunogenicity substudy. At selected vaccination centres, we collected venous blood samples (5 mL per visit for adults and children aged 6–17 years and 2.5 mL per visit for children aged 4–5 years) from consenting participants at the dose 2 visit and 21 days later (window −3/+7 days). We made 0.5 mL serum aliquots, which were stored at −20°C in the L’Institut National de Recherche Biomédicale (INRB) laboratory in Goma. One aliquot was shipped to Q2 Solutions in the USA for measurement of IgG binding antibodies to EBOV GP by FANG ELISA. The remaining aliquots are being stored in Goma until the end of study and will then be destroyed. We provided participants with an immunogenicity subset attendance card with a photograph and ID number for identification at the 21 days post dose 2 visit. We deferred blood drawing if participants were unwell at the second visit. Enrolment and site visits of this subset were completed on 7 December 2020. Details of laboratory handling of biological specimens can be found in the Laboratory Analytical Plan.Safety subset: 1000 participants (approximately 500 adults and 500 children predose 1) were asked to consent to a telephone call at 1 month post dose 2 to collect data on SAEs.Pregnancy subset: up to 500 pregnant participants (250 pregnant predose 1 and 250 pregnant within 30 days of dose 2) were asked to consent to receive telephone calls to collect SAEs at D7 and D21 post dose 1, and at D7, 1 month, 3 months and 6 months post dose 2 (unless delivery has occurred before these time points) and data are being collected on pregnancy outcomes as described below.

### Safety measurements

Following each vaccination, we gave participants instructions to contact the study team for any SAEs occurring up to 1 month post dose 2 and where to seek care for medical problems, including antenatal care for pregnant women (table 3). Whenever possible, we documented the diagnosis or syndrome related to SAEs, rather than multiple symptoms. Investigators then assessed any potential causal relationship to vaccination. We followed up SAEs to resolution or stabilisation, irrespective of severity or whether considered vaccine related. We allowed unscheduled study follow-up visits on adverse events at the investigator’s discretion.

Follow-up of pregnant women is ongoing. We compiled a registry of pregnant women and we encouraged women who become pregnant within 1 month of any vaccine dose to contact the team. We are telephoning all known pregnant women 1–3 months after delivery to record birth outcomes or, when possible, a study clinician visits them in person if they are not contactable by telephone. In the pregnancy subset, we actively follow by telephone 250 women who were pregnant at the time of dose 1 and up to 250 who became pregnant within 30 days (1 month) of administration of either dose 1 or 2. We make calls to collect SAE data at D7 (−3/+7 day) and D21 (−6/+7 day) post dose 1, D7 (−3/+7 day) post dose 2, and at 1 month (−7 day/+1 month), 3 months (±14 day) and 6 months (−14/+28 day) post dose 2 (unless delivery occurs before these time points). We are performing a clinical examination on the first 100 infants born to women in the pregnancy subset at around 3 months of age (ranging from 1 to 6 months). We offer a small bag of rice, cassava or equivalent to mothers returning to the clinic for infant safety follow-up visits.

In the safety subset, we actively followed the first 500 adults and first 500 children enrolled by telephone 1 month (−7 days/+1 month) after administration of dose 2.

For acute medical problems, we provide care to participants with referral to health clinic and hospitals as necessary. The trial sponsor and funder have put in place global and local clinical trial insurance covers to compensate any potential harm to participants.

### Social science methods

We are using multiple modalities to explore the socioeconomic and sociocultural contexts of EVD and the study, including perception of illness and disease, trust in medical research and the motives for the study, key community dynamics and power relations, barriers and opportunities. This information can be used to trace any ongoing rumours and concerns emerging at the community level and to provide appropriate feedback to the study team.

The social science component of the study includes the following:

30 in-depth interviews: 5 women, 5 men, 5 girls and 5 boys aged 12–17 years old and 10 parents/care providers of children aged 1–11 years, post dose-1 or 2.Eight focus group discussions: including adult participants, parents of children aged 1–11 years, and boys and girls aged 12–17 years.Up to 10 key informant interviews: local and national stakeholders.Participant exit interviews at vaccination visits to document immediate concerns related to clinic experiences.Ethnographic observation in study clinics and key sites (eg, markets, motorbike parking grounds).

At the beginning of all interviews, the social science team ask participants to state that they consent to taking part, recording this both digitally and by hand on the consent form, or only by hand if permission is not given for digital recording. Parents are being asked to provide consent for children under 17 years and children aged 12–17 years to provide assent. Interviews are being conducted in the participant’s/parent’s/guardian’s primary language. Exit interviews are extremely basic and rapid and simply record whether participants had any immediate concerns they wished to report. If in-person interviews are not possible, we conduct phone interviews with adult participants, with researchers reading out information from an information sheet.

Interviews are conducted in French, Swahili or Nande and then translated to English. We remove personal identifiable information prior to uploading recordings to a SharePoint which is only accessible to the study team. We give each interview participant a unique ID number and delete their phone numbers from study databases immediately after use.

## Outcomes

The primary study outcomes are:

1) The numbers and odds of vaccination status in EVD cases and in EVD-negative controls in a test-negative case-control study with a target sample size of 110 laboratory confirmed EVD cases matched to controls who test negative for EVD. Effectiveness is derived from the OR for vaccination in cases compared with controls to calculate VE.

The secondary outcomes include:

The number and proportion of adults and children with solicited and unsolicited SAEs from the date of first vaccination to 1 month post dose 2. Data on SAEs within 1 month post dose 2 that are considered related to vaccination with Ad26.ZEBOV, MVA-BN-Filo in adults and children.The number and proportion of adults and children receiving dose 1.The number and proportion of adults and children receiving dose 2.The number of participants participating in in-depth interviews and focus group discussions on participant and community perceptions of the trial and on vaccine acceptability.

The exploratory outcome includes:

The level of IgG antibodies against EBOV GP in samples collected from participants in the immunogenicity subset who received dose 2 outside the recommended interval between dose 1 and dose 2.

## Data collection, management and analysis

### Data collection

Data collection is ongoing. We collect data using electronic case record forms (eCRFs) developed using Open Data Kit (ODK) software on password protected tablets, and on standardised paper CRFs when eCRF use is not possible.^28^ We designed a modular system of ODK forms in English and French to collect data on different aspects of the study, including consent, vaccinations and errors on eCRF completion. Prior to starting the study, we provided and reviewed guidelines for CRF completion with study site personnel. Automated programmes in R or STATA summarise study progress and create line-lists for follow-up and dose 2 visits, and to identify errors. Data can be exported as delimited text files. Automated checks ensure data completion. Study team members receive daily updates and reports via a password protected dashboard. eCRFs are also transferred into REDCap Good Clinical Practice (GCP) compliant software for an audit trail of data cleaning. Data collected in paper-based CRFs are double-entered directly into a REDCap database.

After encryption, data are sent via end-to-end encrypted https protocols to a server hosted at the London School of Hygiene & Tropical Medicine (LSHTM), with ongoing transfer of data to servers hosted by INRB and Epicentre via SSH File Transfer Protocol. Only the data management team at Epicentre and INRB are able to decrypt the raw data. Study personnel save, store, back-up, transfer and share data in encrypted file formats and over encrypted transmission routes. To the extent possible, we use deidentified data for operational and analytic purposes. Permissions to decrypt data are limited to key personnel. Working copies of databases such as those used by staff who are responsible for progress monitoring and statistical analysis are automatically stripped of personal identification data via a process applied by data managers at Epicentre.

We anonymise interview transcripts and field notes and download them to password protected and encrypted computers for transcription and translation and analysis using NVIVO software. We keep all recordings, transcripts and field notes in locked filing cabinets at the study’s Goma data centre, before moving them to the long-term archive at INRB Kinshasa. Details of database validation, data collection, coding, security, automatic, query, cleaning and safety data reconciliation can be found in the Data Management Plan.

### VE analysis

We define cases (test-positives) as laboratory-confirmed EVD cases as per DRC Ministry of Health centralised reporting and controls (test-negatives) as those with suspected EVD but whose laboratory tests were negative. Prior to the end of the outbreak, we envisaged that identification of controls would be retrospective, blind to vaccination status, on individuals residing or working in areas that were offered vaccination prior to presentation with symptoms at health facilities, with geographical matching to allow cases and controls to have had equal opportunities to have been vaccinated. Frequency matching or adjustments using regression techniques for other characteristics such as age, sex and possibly also exposure to EBOV were to be described in the Statistical Analysis Plan.

Since the likely ratio of test-negatives to test-positives at screening centres was unknown, it was recognised that, if a high number of individuals with a very low percentage of confirmed cases presented in a short period of time, random sampling of test-negatives on a frequency matched basis may be required.

If the duration of Ebola outbreak had permitted measurement of VE, individuals who received rVSV-ZEBOV-GP, or the first but not the second dose of Ad26.ZEBOV, MVA-BN-Filo or who received the second dose less than 21 days prior to testing for EVD would have been excluded from the primary analysis.

For the primary analysis, the odds of having been fully vaccinated (having received the two doses, in the right order, at least 1 month apart, at least 21 days before the onset of symptoms) would have been compared with the odds of not being vaccinated between the cases and controls through the OR, providing an estimate of VE: (VE (%)=(1–OR)×100), with regression analyses allowing for appropriate account of any matching and adjustment for potential confounders.

We also planned to examine VE of at least one dose of the vaccine and development of disease within 21 days after the second dose as secondary analyses.

### Safety analysis

Safety analyses will include all participants receiving at least dose 1. We will summarise the incidence of SAEs overall, by time since vaccination and by age and whether or not vaccination was received during pregnancy. The incidence of SAEs will also be tabulated by MedDRA preferred term and system organ class (Medical Dictionary for Regulatory Activities version 23.1).

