After the VE analysis had been conducted based on 110 cases, the study team planned discussions to review the findings and the value of continuing to enrol participants.

Two subsets of individuals, 1000 vaccinated individuals (500 adults and 500 children) and 500 pregnant participants (250 pregnant predose 1 and 250 pregnant within 30 days of dose 2), were enrolled for more active follow-up for safety reporting (table 3). The sample size allowed for 95% probability to detect at least one vaccine related serious adverse event (SAE) if the true incidence of that SAE is at least 1.2% with 250 individuals, 0.6% with 500 individuals, or 0.3% with 1000 individuals.

**Table 3 T3:** Time and event schedule for intervention delivery and safety evaluations

Preparation	Up to 1 month before study starts	D0 Dose 1 visit	D7 (−3/ +7 day)	D21 (−6/ +7 day)	D56 Dose 2 visit (−14/+28 day)	D7 post dose 2 (−3/ +7 day)	D21 post dose 2 (−3/+7 day)	1 month post dose 2 (−7 day/+1 month)	3 months post dose 2 (±14 day)	6 months post dose 2 (−14/+28 day)	3 months post delivery
Mapping and selection of study sites	X										
Community engagement and social mobilisation	X										
Consent, vaccination dose 1		X									
Vaccination dose 2					X*						
SAE assessment					X**†**			X‡			
Safety subset					X			X§			
All pregnant women					X**¶**			X			X**
Pregnancy subset		X	X††	X††	X	X††		X††	X††	X††	X‡‡
Immunogenicity subset					X§§		X§§				

*Dose 2 may be given between D42 and D84. Participants who return for dose 2 after 84 days will still be vaccinated.

†D56 safety data are collected at dose 2 visits.

‡Passive serious adverse event (SAE) recording from main study participants through participant-initiated phone calls or other contact with team, until 1 month post dose 2.

§Safety subset: 1000 participants will be actively followed up for SAEs by phone at 1 month post dose 2.

¶If study vaccinations have been paused, all pregnant participants who have not received dose 2 will be called at D56 (±7 days) to collect safety data.

**All pregnant women will have their birth outcomes collected around 3 months post delivery (between 1 and 3 months). When feasible, team to visit if the woman is not contactable by telephone.

††Pregnancy subset: safety telephone calls to collect SAEs at D7 and D21 post dose 1, and then at D7, 1 month, 3 months and 6 months post dose 2, unless delivery is before these time points.

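### SAE incidence pools self-reported and actively elicited events, so the overall figure is likely understated and the pregnancy breakdown is confounded with how SAEs were found

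*Protocol article*

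**What the plan says.** The Safety analysis section defines one set: "Safety analyses will include all participants receiving at least dose 1". It then states the summary: "We will summarise the incidence of SAEs overall, by time since vaccination and by age and whether or not vaccination was received during pregnancy". The Outcomes section defines the SAE outcome as a number and proportion that combines solicited and unsolicited events, from first vaccination to 1 month post dose 2. Intervention delivery gives the size of the set: "20 427 participants had been vaccinated".

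The footnotes to Table 3 show that SAEs are found in different ways:

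- Main study: "Passive serious adverse event (SAE) recording from main study participants through participant-initiated phone calls or other contact with team", up to 1 month post dose 2. In addition, "D56 safety data are collected at dose 2 visits".
- Safety subset: "1000 participants will be actively followed up for SAEs by phone at 1 month post dose 2".
- Pregnancy subset (up to 500 women): "safety telephone calls to collect SAEs at D7 and D21 post dose 1, and then at D7, 1 month, 3 months and 6 months" after dose 2, unless delivery comes first.
- Pregnant women in general: birth outcomes are collected after delivery. If vaccination is paused, "all pregnant participants who have not received dose 2 will be called at D56". Table 3 also marks an assessment at 1 month post dose 2 in the row for all pregnant women, without a footnote on how it is done.

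**The concern.** A proportion with SAEs can be interpreted only if the events in its numerator were looked for in a similar way across its denominator. Here the intensity of looking is tied to one of the variables that the table is broken down by. Women vaccinated in pregnancy are the group most likely to be telephoned, and telephoned repeatedly. Most other participants must make contact themselves or be asked at the dose 2 visit.

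Two results are affected. The overall incidence mixes a small, well-observed group with a large, mostly self-reporting one, so it probably falls below the true value. In the pregnancy breakdown, two adjacent incidences would differ even if the true risks were the same, and readers will compare them whether or not a test is planned. The pause in vaccination from 10 April to 14 September 2020 adds to this. For those it caught, it delayed the one contact common to all groups, the dose 2 visit, and Table 3 lists a substitute call for pregnant women only.

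**Working it through.** **The plan's own safety figure.** The Sample size section gives a 95% probability of seeing at least one event. With P = 1 − (1 − p)^n:

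- n = 250, p = 1.2%: 95.1%
- n = 500, p = 0.6%: 95.1%
- n = 1000, p = 0.3%: 95.0%

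These reproduce. The formula takes every SAE as captured. If half were captured (p replaced by 0.5p), the probability would be about 78% in each case.

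**Share outside active follow-up.** Assume the subsets are full and do not overlap: 20 427 − 1000 − 500 = 18 927, and 18 927/20 427 = 92.7%.

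**Pooled incidence as a share of the truth.** The documents give no capture rates, so the rates here are assumptions: 90% with active calls, and s with self-report plus the dose 2 visit. Pooled capture = (1500 × 0.9 + 18 927 × s)/20 427.

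**Pregnancy breakdown with equal true risk.** Take 250 women vaccinated in pregnancy, all in the pregnancy subset. The other 20 427 − 250 = 20 177 include 1250 actively followed people: 1000 in the safety subset and up to 250 in the pregnancy subset who conceived around vaccination. Expected ratio = 0.9 / [(1250 × 0.9 + 18 927 × s)/20 177].

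**The same with half of the pregnant women outside the subset.** Take 500 vaccinated in pregnancy, 250 of them actively followed. The remaining 19 927 have 1250 active and 18 677 passive. Expected ratio = [(0.9 + s)/2] / [(1250 × 0.9 + 18 677 × s)/19 927].

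| Assumed passive capture s | Pooled incidence / truth | Ratio, all pregnant women active | Ratio, half active |
|---|---|---|---|
| 60% | 12 706/20 427 = 62% | 0.9/0.619 = 1.5 | 0.75/0.619 = 1.2 |
| 30% | 7028/20 427 = 34% | 0.9/0.337 = 2.7 | 0.60/0.338 = 1.8 |
| 15% | 4189/20 427 = 21% | 0.9/0.196 = 4.6 | 0.525/0.197 = 2.7 |

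The ratio is 1.0 only if passive capture equals active capture. A contrast limited to actively followed people also has an expected ratio of 1.0 when capture is equal. Up to six calls against one leaves some imbalance. Four of the six (D7 and D21 post dose 1, D7 and 1 month post dose 2) fall within the outcome window.

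**The case against.** The strongest reply is that this is a short descriptive paragraph in an article. It says SAEs will be summarised and names no test, ratio or difference. Detail on analysis populations, data handling and subgroups is referred to a SAP that is not shown and may split results by surveillance mode. A safety set of everyone dosed is conventional, and the detection limits for 250, 500 and 1000 people suggest some reporting by subset. All of this stands as a limit on how strongly the point can be put, and the absence of a split from the article is not itself the fault. The point rests on what the text commits to: one proportion that combines solicited and unsolicited events, tabulated by pregnancy. A further split in the SAP would not make that figure interpretable.

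A reader might infer four stronger things that the documents do not support:

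- **That a formal pregnancy comparison is planned and is driven by detection.** None is stated, and without capture rates the bias could be small. Confounded is the right word.
- **That everyone not pregnant is a passive reporter, so the ratio is simply 0.9/0.3 = 3.0 or 0.9/0.15 = 6.0.** The safety subset is called, and dose 2 attenders give safety data at the visit. Counting the 1250 actively followed others brings these to 2.7 and 4.6.
- **That pregnancy-subset SAEs accrue over a longer period within the outcome.** The Outcomes section and Table 1 both end the SAE outcome at 1 month post dose 2, so events after that fall outside it.
- **That the trial claims comparative safety in pregnancy.** The strengths list claims only to be the first to give the regimen to pregnant women.

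**Conclusion.** The point holds as a moderate reporting and analysis fix. As written, the text yields an overall SAE incidence that is probably too low and a pregnancy breakdown that cannot be separated from how events were found. The direction rests on one assumption, that scheduled calls find more SAEs than self-report plus the dose 2 visit. The size is unknown. With equal true risk, the illustrative ratio is 1.5 to 4.6 if all women vaccinated in pregnancy are actively followed, and 1.2 to 2.7 if half are. Pooled incidence would be 62% to 21% of the truth over the same range of assumed passive capture. These figures also assume full, non-overlapping subsets and the same 90% capture whether a person has one call or six.

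**What to change.** In the Safety analysis section:

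1. Report SAE incidence separately for the passively followed main study, the safety subset and the pregnancy subset. In the two active subsets, use participants actually reached as the denominator.
2. Take the incidence estimate from the active subsets, and present main-study SAEs as reported counts and rates. The safety-subset call is timed from dose 2, so say that this estimate describes dose 2 recipients who were reached.
3. Report all pregnancy-subset SAEs, with those after 1 month post dose 2 shown separately.
4. Limit any pregnancy contrast to actively followed participants up to 1 month post dose 2. Label it descriptive and state the imbalance of up to six calls against one. Otherwise, give pregnancy SAEs without a comparator. If a contrast leaves out in-window events found only at the D7 or D21 calls, label it so, and never drop those events from the reported pregnancy SAEs.
5. Reconcile who counts as the second pregnancy group. Sample size and Intervention delivery tie it to dose 2, whereas Safety measurements says either dose. This affects who is tabulated as vaccinated during pregnancy.

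The change needs no new data, only analysis wording and a table split. The cost is precision. With 1000 people and no events, the upper 95% limit is about 3/1000 = 0.3%, and a pregnancy contrast would rest on a few hundred people per group at most.
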